
## 2.2 OBJECTIVES

### 2.2.1 Objectives and research questions

The objective of the present study is to compare the musculoskeletal function between ACL reconstructed individuals with and without knee pain to answer the research question: Are there differences in the musculoskeletal function in ACL reconstructed individuals with knee pain when compared to those without knee pain?

The musculoskeletal function will be assessed by

- Muscle strength of the knee extensor muscle (quadriceps)
- Biomechanics of the knee and quadriceps muscle during walking and a forward lunge movement

### 2.2.2 Hypotheses

- 1) ACL reconstructed individuals without knee pain have stronger quadriceps muscles compared to those with knee pain.
- 2) ACL reconstructed individuals without knee pain develop higher quadriceps muscle forces and knee joint loading during walking and forward lunging compared to those with knee pain.

### 2.2.3 Scope

This SAP is structured as recommended for observational studies. It will be the guiding document for the main analyses testing the two hypotheses and will exclusively include outcomes obtained from the ACL reconstructed leg (see section 6.1.1).

The data obtained from the participants' contralateral (i.e. non-operated) leg will be reported in subsequent sub-studies with separate SAP documents.

## 3.0 STUDY METHODS

### 3.1 GENERAL STUDY DESIGN AND PLAN

This is a cross-sectional observational study. Two groups of ACL reconstructed individuals identified as symptomatic (with knee pain) and asymptomatic (without knee pain) are invited to participate in the study that takes place at The Parker Institute/Bispebjerg-Frederiksberg Hospital, Copenhagen, Denmark. The study protocol (APPI2-PT-2020-02) was written and approved by the local ethics committee before study initiation. The final protocol (version 1.2) is published on the Parker Institute's website. This SAP was written after the initiation of the data collection (June 2021) and finalized before the inclusion of the last participant. The author of the SAP was not blinded to the database during writing the SAP. However, data were not summarized or analyzed before completing the SAP.

### 3.2 SAMPLE SIZE, POWER AND DETECTABLE DIFFERENCE

We will compare the quadriceps muscle strength between two groups of ACL reconstructed individuals: 1) symptomatic and 2) asymptomatic.

The variance in this population is unknown, while our sample size estimation will be pragmatic. To detect a group difference of 0.3 Nm/kg in the primary outcome with a common standard deviation of 0.5 Nm/kg, a sample size of 50 per group will have a power of 84%, ( $\alpha = 0.05$ ). Thus, a total sample size of  $n=100$  (50/50 per group) was originally intended to be applied. However, in November 2021 71 (17/54 symptomatic/asymptomatic) participants were recruited and included in the study, indicating a low prevalence of symptomatic participants. We estimated that it would be difficult to recruit

## STATISTICAL ANALYSIS PLAN: MIRAKOS

50 symptomatic participants within the time allotted for recruitment (scheduled to last until August 2022). In contrast, the recruitment of participants to the asymptomatic group has proven to be efficient. Therefore, we decided to re-calculate the sample size and change the group allocation ratio from 1:1 to 1:3. To detect that same group difference with the same common standard deviation of the primary outcome as stated above, a new total sample size was estimated to  $n=120$  ( $n=30$  symptomatic and  $n=90$  asymptomatic participants) with a statistical power of 80.6%. This amendment was registered in the study protocol 4th November 2021. Currently, our goal is to continue the data collection until the inclusion of 120 eligible participants (symptomatic/asymptomatic;  $n=30/90$ ) is reached. However, the inclusion of participants will end in August 2022, leaving some uncertainty about the final sample size.

### 3.3 TIMING OF FINAL ANALYSIS

The final analysis will be done after 31/8 2022 but no later than 31/12 2022 and presupposes that the inclusion of participants has ended, all data have been collected and the database has been closed. The SAP will be published on the Parker Institute's website along with the study protocol before any data analyses are conducted.

### 3.4 TIMING OF OUTCOME ASSESSMENTS

The processing of motion capture data and musculoskeletal modelling to provide biomechanical variables is time-consuming and will be done after the measurement visit of each participant. Thus, the outcomes to assess the knee and quadriceps muscle function during walking and forward lunge movement are generated continuously and registered in the database during the data collection period. This will continue for a short period after the inclusion of the last participant. All other outcomes and data are registered in the database at or immediately after the measurement visit. The participants fill out electronic-format questionnaires for assessment of self-reported knee function at the measurement visit and these data are registered directly in the database. While the research team will not be blinded to the data, there will not be any data extraction before the data collection has ended/the database closed and the SAP has been finalized.

## 4.0 STATISTICAL PRINCIPLES

### 4.1 MULTIPLICITY

We will not adjust for multiplicity. We are fully aware that the risk of type I error is present as we will make many comparisons and our outcomes are very likely correlated. Thus, we will explicitly state that the analyses are exploratory and hypothesis-generating and that the results may need replication in studies with a more causal design.

### 4.2 STATISTICAL SIGNIFICANCE AND CONFIDENCE INTERVALS

A P-value  $< 0.05$  are considered statistically significant for our primary outcome. Results will be reported as mean values with standard deviation (SD), or group mean differences with a 95% confidence interval (CI).

### 4.3 ADHERENCE AND PROTOCOL DEVIATIONS

#### 4.3.1 Definitions of protocol deviations

Protocol deviations are defined as study activities that diverge from the local institutional review board reviewed protocol but without significant consequences.

## STATISTICAL ANALYSIS PLAN: MIRAKOS

### 4.3.2 Protocol deviations to be summarised

The following deviations from the protocol have been identified:

- The pressure pain sensitivity was assessed by *two* pressure pain thresholds: 1) the pressure pain detection threshold (PDT) and 2) the pressure pain tolerance threshold (PTT). The PTT defines the pressure, at which the pain becomes intolerable (section 6.2.7).
- The current knee pain was assessed by a verbal rating scale (VRS) 0-10 *both* during walking/forward lunging *and* during the muscle strength testing, meaning that after each walking/lunging/contraction trial the participant verbally rated the current knee pain on a 0-10 VRS (section 6.2.9).
- The knee joint laxity testing was part of the clinical examination *but* an instrumented knee joint laxity test was also done during the experiments to quantify the laxity and report it as a participant characteristic (section 6.2.10).
- The second hypothesis was originally formulated: “ACL reconstructed individuals without knee pain develop higher quadriceps muscle forces and knee joint compressive forces during walking and forward lunging compared to those with knee pain”. This has been refined: “ACL reconstructed individuals without knee pain develop higher quadriceps muscle forces and knee joint loading during walking and forward lunging compared to those with knee pain”. The reason for this change is that we assess *both* the knee joint compressive force *and* the knee extensor moment and these two parameters are covered under “knee joint loading”.

The above was either not explicitly stated in the study protocol or reflects refinements to its content.

This SAP focus on measurements from the ACL reconstructed leg while observations from the contralateral leg will be reported in subsequent sub-studies (section 2.2.3).

## 5.0 STUDY POPULATION

### 5.1 SCREENING DATA

Screening data were collected with the purpose to describe the eligibility of all potential participants responding positively to the study invitation letter (see section 5.3). Thus, reasons for non-eligibility will be documented, and includes (but are not limited to):

- Major surgery to the other knee, e.g., ACL reconstruction.
- Other musculoskeletal pain in the lower extremities.
- BMI > 30.
- Neuromuscular diseases.

### 5.2 ELIGIBILITY

The aim was to compare participants with and without knee pain, the eligibility criteria were as follows:

Participants with knee pain (“Symptomatic group”):

Inclusion criteria:

- Age between 18 and 40 years at the time of ACL reconstruction.
- Primary ACL reconstruction using the semitendinosus-gracilis tendon graft.
- Post-surgery time of at least 3 years.

## STATISTICAL ANALYSIS PLAN: MIRAKOS

- Current body mass index (BMI) of  $\leq 30$ .
- Pain score of at least 3 (VRS 0-10) in the reconstructed knee during activities of daily living (ADL) within the last week.

Participants without knee pain (“Asymptomatic group”):

Inclusion criteria:

- Age between 18 and 40 years at the time of ACL reconstruction.
- Primary ACL reconstruction using the semitendinosus-gracilis tendon graft.
- Post-surgery time of at least 3 years.
- Current body mass index (BMI) of  $\leq 30$ .
- Pain score of 0 (VRS 0-10) in the reconstructed knee during activities of daily living (ADL) within the last week.

For both groups, the exclusion criteria are the same:

Exclusion criteria:

- Known neuromuscular diseases.
- Evidence of cartilage lesions ICRS grade 4 (full thickness) from MRI at time of ACL reconstruction or documented peri-surgically.
- ACL reconstruction or other major surgery to the other knee.
- Congenital deformities in the lower extremities preventing full participation in the tests.
- Current musculoskeletal pain in other regions of the lower extremity other than the injured knee.
- Any other condition that in the opinion of the investigator makes a potential participant unfit for participation or conditions that puts a potential participant at risk by participation.

### 5.3 RECRUITMENT

ACL reconstructed persons were identified in the Danish Ligament Reconstruction (DLR) Register and invited to participate in the study by sending them an invitation letter via digital mail (e-Boks) stating the main criteria for participation. A flow diagram will be used to visualize the flow of participants. Here we will report the population identified in the DLR register and from where eligible participants were selected, reasons for exclusions and how many were included and allocated to the symptomatic and asymptomatic group and any withdrawals. See figure 1 for an example.

### 5.4 WITHDRAWAL/FOLLOW-UP

This study is a cross-sectional observational study with no interventions applied. Thus, we expect the withdrawal rate to be negligible. Withdrawal can occur when the eligible participants refuse to participate or if other issues emerge preventing the participant from participating in the experiments after written informed consent has been obtained.

### 5.5 BASELINE PARTICIPANT CHARACTERISTICS

#### 5.5.1 Collected baseline participant characteristics

Most of the data are collected at the measurement visit (one day) while only a few clinical data are extracted from electronic registry databases (e.g. DLR Register or patient record via the electronic medical journal “Sundhedsplatformen” (SP)) and few participants characteristics are registered during screening. Table 1 displays an overview of all the collected variables.

## 5.6 ASSUMED CONFOUNDING COVARIATES

Although, we cannot exclude that our measured variables may be influenced by measured and un-measured variables (e.g. genetic, environmental, psychological) that potentially confound the interpretation of the results leading to wrong conclusions, we have not been able to identify any covariates that clearly would influence *both* the exposure (presence of knee pain) *and* outcome (musculoskeletal function). Thus, no adjustments for confounding covariates will be applied in our statistical analyses.

## 6.0 ANALYSIS

### 6.1 OUTCOME DEFINITIONS

The analysis of our primary and secondary outcomes shall answer the research question and test the two hypotheses (see section 2.2).

#### 6.1.1 Study knee

The study knee is defined as the knee at which the ACL was reconstructed. The outcomes are obtained from the participants' study knee and used as input parameters to the statistical analyses (section 6.3).

#### 6.1.2 Primary outcome

The primary outcome is the maximal isometric quadriceps muscle strength defined as the highest torque value measured among three separate maximal voluntary isometric contraction (MVIC) repetitions. The unit for the primary outcome is Nm/kg (see section 6.2.1).

#### 6.1.3 Key secondary outcomes

The following outcomes are assessed as key secondary outcomes:

- The peak knee extensor moment during walking defined as the mean of the individual peak knee extensor moment values across six walking trials. The unit for this outcome is Nm/kg (section 6.2.2).
- The peak knee extensor moment during the forward lunge defined as the mean of the individual peak knee extensor moment values across three forward lunge trials. The unit for this outcome is Nm/kg (section 6.2.2).
- The peak quadriceps muscle force during walking defined as the mean of the individual peak quadriceps muscle force values across six walking trials. The unit for this outcome is N/kg (section 6.2.2).
- The peak quadriceps muscle force during the forward lunge defined as the mean of the individual peak quadriceps muscle force values across three forward lunge trials. The unit for this outcome is N/kg (section 6.2.2).
- The peak knee joint contact force during walking defined as the mean of the individual peak knee joint contact force values across six walking trials. The unit for this outcome is N/kg (section 6.2.2).
- The peak knee joint contact force during the forward lunge defined as the mean of the individual peak knee joint contact force values across three forward lunge trials. The unit for this outcome is N/kg (section 6.2.2).

#### 6.1.4 Other secondary outcomes

The following outcomes are assessed as other secondary outcomes:

- The current knee pain during the hamstring muscle strength test defined as the mean of the individual VRS scores reported after three MVIC trials (section 6.2.9).

## 6.2 MEASUREMENTS AND CALCULATION OF OUTCOMES

### 6.2.1 Muscle strength

MVICs of the quadriceps and hamstring muscle strength will be assessed using an isokinetic dynamometer (Biodex System4 Pro, Biodex Medical System, NY, USA) at 60° knee flexion. The participants are seated in a rigid chair firmly strapped to the seat across the chest, at the hip and distal thigh. The rotation axis of the dynamometer is visually aligned to the lateral femoral epicondyle and the lower leg attached to the lever arm of the dynamometer. The lever arm is placed just above the lateral malleolus and firmly fixed with a cuff. The participants are asked to perform the MVICs with maximal effort and verbal encouragement will be provided during testing that comprises three repetitions

## STATISTICAL ANALYSIS PLAN: MIRAKOS

of which the highest peak torque value defines the maximal quadriceps/hamstring muscle strength and will be reported as body mass normalized values (Nm/kg).

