## 7.3 MUSCLE STRENGTH TEST

Isometric quadriceps and hamstring muscle strength will be assessed using an isokinetic dynamometer (Biodex System4 Pro, Biodex Medical System, NY, USA). The dynamometer records the torque (Nm) produced by isometric muscle contractions. The participants are seated in a rigid chair firmly strapped to the seat at the hip and distal thigh. The rotation axis of the dynamometer is visually aligned to the lateral femoral epicondyle and the lower leg attached to the lever arm of the dynamometer. The lever arm is placed just above the lateral malleolus and fixed with a cuff. Prior to testing, 15 min. of warm-up will be applied to familiarize the subjects to the dynamometer and the test procedures. Maximal voluntary isometric contractions (MVICs) of the quadriceps and hamstrings, respectively, will be done at 60° knee flexion. The participants are asked to perform the MVICs with maximal effort and verbal feedback and encouragement will be provided during testing that comprises three repetitions of which the highest peak torque value will be defined as the maximal quadriceps/hamstring muscle strength and reported as body mass normalized values (Nm/kg).

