## 8.0 STATISTICAL CONSIDERATIONS

### 8.1 SAMPLE SIZE

We will compare the quadriceps muscle strength between two groups of ACL reconstructed individuals: 1) with and 2) without knee pain.

The variance in this population is unknown, while our sample size estimation will be pragmatic. To detect a group difference of 0.3 Nm/kg in the primary outcome with a common standard deviation of 0.5 Nm/kg, a sample size of 120 with a 1:3 group allocation ( $n=30$  symptomatic;  $n=90$  asymptomatic) will be required.

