## 2.0 INTRODUCTION

### 2.1 BACKGROUND AND RATIONALE

Knee osteoarthritis (OA) is the most common joint disease and a significant contributor to global disability . The known knee OA risk factors include obesity, surgery, occupational load and injury . Anterior cruciate ligament (ACL) rupture is a common knee injury  and the incidence is increasing, particularly among young people . ACL injury affects the knee joint function and increases the risk of knee OA development  even at a young age, which prolongs the period of impaired function and pain . Most research has focused on radiographic knee OA while fewer studies have investigated the prevalence of symptomatic knee OA after ACL injury . It is important to discriminate between radiographic and symptomatic knee OA, as knee pain is a decisive criterion to diagnose knee OA , whereas radiographic changes serve more as a confirmatory measure. Indeed, the Framingham study showed that the prevalence of radiographic changes (indicative of OA) in the population older than 63 years was 33% whereas the prevalence of symptoms was only 9% . A recent MRI study of 230 asymptomatic knees reported that 97% of these showed abnormalities in at least one knee structure . This emphasizes that image-based signs of knee OA are not always accompanied by pain and OA symptoms.

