#### The modeling and simulation workflow

Modeling and simulation were performed in OpenSim (version 4.1)  utilizing the standard algorithms of the software. The model was scaled to match the dimensions of the individual using hip, knee, and ankle joint centers estimated from star-arc and squatting tasks, respectively using SCoRE and SARA algorithms implemented in Vicon Nexus . Intercondylar distance (i.e., the frontal plane distance between the contact points at the medial and lateral tibiofemoral joint) was set based on the mediolateral distance between the midpoints of femoral condyles measured from radiographs using an approach based on automatic anatomical landmark localization of bones . Optimal forces of the muscles (representing muscle strength) were scaled relative to the mass of the participant with allometric scaling  as done previously . We additionally increased the optimal forces with a factor of 1.5 to ensure that the model was able to produce the high joint moments measured in forward lunging (equation 1).

$$\text{Optimal force scaling factor} = 1.5 * \left( \frac{\text{SUBJECT MASS}}{\text{GENERIC MODEL MASS}} \right)^{\frac{2}{3}} \quad (1)$$

Subsequently, to account for the participant-specific muscle strength deficit of the ACL-reconstructed leg in knee flexion and extension often present in ACL reconstructed individuals , we adjusted the optimal forces of the model's quadriceps and hamstring muscles in the reconstructed limb with a scale factor (common for the muscle group) that replicated the experimentally measured interlimb difference in muscle strength (joint moment) at the same joint configuration in which the experimental test was performed while maximally activating the quadriceps/hamstring muscles.

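### Quadriceps strength is analysed only as torque per kilogram, so a difference in body mass between the groups could show, or hide, a difference in the primary outcome

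*Combined protocol and SAP*

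**What the plan says.** Hypothesis 1 (SAP 2.2.2) is that "ACL reconstructed individuals without knee pain have stronger quadriceps muscles compared to those with knee pain". It names no scale. The rationale in SAP 7.0 is about the muscle: quadriceps weakness, and the effect of knee pain on activation and force production.

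The outcome is a ratio throughout. SAP 6.1.2 states: "The unit for the primary outcome is Nm/kg". Under SAP 6.2.1 the highest peak torque of three contractions "defines the maximal quadriceps/hamstring muscle strength and will be reported as body mass normalized values (Nm/kg"). Protocol 7.3 has the same rule, with strength "reported as body mass normalized values (Nm/kg") and a reference on normalisation for body size. The sample size uses the same scale: "To detect a group difference of 0.3 Nm/kg in the primary outcome" (protocol 8.1).

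Table 3 lists quadriceps and hamstring strength in Nm/kg only, although the dynamometer records Nm. SAP 5.6 rules out adjustment for confounding covariates, so body mass enters the primary test only as the divisor. Table 2 compares height, body mass and BMI between the groups. BMI must be 30 or less in both, and the groups are not matched on mass.

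**The concern.** A ratio to body mass fixes the relation between torque and mass at exact proportionality. Kilograms that bring less torque than that lower Nm/kg with no change in the muscle. If one group is heavier and proportionality fails, the divisor alone produces a group difference. If the symptomatic group is lighter, the divisor can cover a real torque deficit.

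At stake is the wording of the main conclusion. A significant result in Nm/kg would be read as support for Hypothesis 1, a statement about muscle, when it might be a statement about weight. Table 2 would flag a mass imbalance, but it would not estimate how much of the strength difference that imbalance explains.

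**Working it through.** **Inputs from the documents.** Target difference 0.3 Nm/kg, SD 0.5 Nm/kg, 30 symptomatic and 90 asymptomatic, alpha 0.05 (protocol 8.1; SAP 3.2 and 6.3.1).

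**Inputs assumed, not in the documents.** Asymptomatic mean r = 2.8 Nm/kg (range 2.5 to 3.0) at mass m0 = 75 kg; symptomatic group 5 kg heavier (range 3 to 8); SD unchanged.

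**1. The plan's own power.** SE = 0.5 × √(1/30 + 1/90) = 0.105 Nm/kg. With a two-sided t test on 118 degrees of freedom and noncentrality 0.3/0.105 = 2.85, power is 80.6%, as stated. The smallest observed difference that reaches P < 0.05 is 1.980 × 0.1054 = 0.209 Nm/kg.

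**2. Spurious difference.** Let torque vary as mass to the power b, and let the groups differ only in mass (m0 asymptomatic, m1 symptomatic). The apparent deficit is r × (1 − (m1/m0)^(b − 1)).

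- b = 1 (proportional): 0 Nm/kg; P < 0.05 in 5% of studies.
- b = 0 (extra mass adds no torque, the upper bound): 2.8 × (1 − 75/80) = 0.175 Nm/kg, which is 0.175/0.3 = 58% of the target; P < 0.05 in 38% of studies.
- b = 0 across the assumed ranges: 2.5 × 3/78 = 0.096 Nm/kg (15% significant) to 3.0 × 8/83 = 0.289 Nm/kg (78% significant).

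**3. Mass excess that brings the expected difference to the threshold, at equal torque.** The deficit for a group heavier by a fraction x is r × x/(1 + x). Setting this to 0.209 gives x = 0.209/(r − 0.209). Over a wider assumed range of means, x is 11.7% at r = 2.0 and 6.3% at r = 3.5, or 8.7 kg and 4.8 kg at 75 kg.

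**4. The opposite direction.** The asymptomatic torque is 2.8 × 75 = 210 Nm. A symptomatic group 5 kg lighter with the same 2.8 Nm/kg has 2.8 × 70 = 196 Nm. If mass does not drive torque, a deficit of 14 Nm (6.7%) is then reported as no difference.

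**5. Would a mass-adjusted torque model help?** In simulations of equal torque, b = 0, a 5 kg gap and an assumed body mass SD of 8 to 12 kg, the ratio was significant in about 40% of studies and the mass-adjusted torque difference in about 5%. Agreement in sign is a weak check: among studies with a spurious significant deficit in Nm/kg, the adjusted estimate had the same sign in 58% to 84%, depending on the mass SD.

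**The case against.** The strongest reply is that nothing here is inconsistent. Protocol, SAP, sample size and Table 3 all define strength as torque per kilogram, with a supporting reference, and Hypothesis 1 is tested through that definition. The SAP also calls its analyses exploratory (4.1 and 7.0). This stands: Nm/kg is not a wrong outcome and should remain primary. It does not settle what a difference in Nm/kg says about the muscle.

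Three stronger readings are tempting, and the documents support none of them.

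- A reader might infer that a heavier symptomatic group with equal torque *would* be found weaker. Even in the extreme case above, a 5 kg gap gives significance in only 38% of studies. No document gives body mass by group. SAP 2.1 says "The known knee OA risk factors include obesity, surgery, occupational load and injury", but that concerns osteoarthritis in general, whereas these groups are defined by pain and share a BMI limit.
- A reader might take the modelling supplement as evidence against proportionality: "Optimal forces of the muscles (representing muscle strength) were scaled relative to the mass of the participant with allometric scaling", with exponent 2/3. That exponent applies to muscle force. Torque is force times moment arm; if lengths scale as mass to the 1/3, torque scales as 2/3 + 1/3 = 1, which is exact proportionality. The supplement is therefore not evidence here.
- A reader might say that the planned tables give no way to see the problem. Table 2 would show a mass imbalance, and mean Nm/kg times mean mass gives a rough group torque. Neither gives an estimate with an interval.

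It may also be said that this repeats the question of covariate adjustment, which SAP 5.6 declines. The two overlap in the remedy. SAP 5.6, however, considers variables that influence both pain and function; here mass is part of the outcome by construction, so that reasoning does not cover whether the divisor fits.

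**Conclusion.** The point holds as a limit on interpretation that the plan can remove cheaply. With torque per kilogram as the only strength measure, the primary comparison cannot separate lower torque from higher mass. On the assumed 2.8 Nm/kg at 75 kg and a 5 kg gap, the effect lies between 0 and 0.175 Nm/kg, and the chance of a significant result with no torque deficit lies between 5% and 38%. The upper figures need extra mass to add no torque at all. The base value, the mass gap and the torque-mass relation are all assumptions. The stated power is correct, and neither the primary outcome nor the sample size needs to change.

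**What to change.** Keep Nm/kg as the primary outcome. Make three additions.

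1. In SAP 6.3.1, one supportive ANCOVA of absolute peak quadriceps torque (Nm) on group with body mass as covariate, reporting the adjusted group difference with its 95% CI. The mass slope is then estimated from the data instead of being fixed at proportionality.
2. In Table 3, a row for that result.
3. A wording rule: a difference in Nm/kg is described as *stronger relative to body mass*. The claim that the quadriceps muscles are stronger is made only if the 95% CI of the mass-adjusted torque difference also excludes zero in the same direction. A point estimate with the same sign is not enough.

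State with SAP 5.6 that body mass enters this model because it is part of the outcome, so that the supportive analysis does not appear to contradict that section. Note also that the model assumes one mass slope for both groups; if the extra mass in one group differs in kind from ordinary variation in mass, some ambiguity remains.

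The cost is SAP wording, one model with one extra degree of freedom and one table row, all from data already recorded. The downside is one more analysis to report and a narrower claim if the two disagree. Power for the Nm analysis cannot be given, because the documents contain no SD in Nm.
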